### Statistical analysis

2.5

For data analysis, the SPSS 20.0 is employed. The patients’ descriptive characteristics are compared using the Chi-square test in the study and control groups. Paired-samples *t* test and independent samples *t* test are utilized to compare the patients’ values between the 2 groups. Variance analysis was utilized to compare the repeated measurements. A *P* < .05 is regarded the significant in statistics.

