### Inclusion of exclusion criteria

2.2

Candidates for inclusion are patients aged 18 to 60 years old with elective LC; ASA I-II classification; and normal platelet coagulation and count function. Exclusion criteria are as follows: patients with potential mental or physical illness; patients with the history of surgery or taking a specific drug; and severe kidney, liver, lung, and heart diseases.

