### Subjects

2.3

Two hundred patients undergoing LC will be included in this study. In the random envelope, all participants will be assigned a random number via utilizing the random number table, and the result of allocation is hidden. Patients are randomly divided into 2 groups: experiential group (n = 100) or control group (n = 100). Physicians, statisticians, data collectors, and evaluators are all blinded to the allocation.

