### Intervention

2.4

The experimental group is given a preoperative nursing visit to each patient 1 day before the operation, whereas the control group not receive preoperative nursing intervention. Preoperative anxiety and the postoperative complications, involving nausea and vomiting, and pain are then investigated for 30 minutes between the experimental group and control group. Anxiety is assessed through utilizing the Spielberger State-Trait Anxiety Inventory,^[13]^ which was translated and then proved in Iranian population. Afterwards, 2 independent psychologists examine the questionnaire for any mistranslation or bias. The questionnaire composes of 20 items and is divided into two 10-question parts to determine trait anxiety or state. It is scored from 1 (no anxiety) to 4 (the highest anxiety level) on the basis of anxiety intensity, with a total score of 20 to 80. The pain is detected utilizing the visual analogue scale. And nausea and vomiting is measured through utilizing the Johnson 10 scale criteria. The data collection involves reviewing the medical records of patients and then performing the face-to-face interviews. Patients in experimental group are interviewed the day before the operation. The interviews contain asking patients about their concerns about surgery plans and procedures, and then answering their questions in easy-to-understand phrases. The patients in experience group also receive education on the surgery team and the environment of operating room, the process of anesthesia, advantages of laparoscopic surgery, and the postoperative care from recovery room to discharge. The primary outcomes include State-Trait Anxiety level and postoperative visual analogue scale. Secondary outcomes included total consumption of analgesics and postoperative complications.

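### Chi-square tests of baseline characteristics do not guard against chance imbalance, and the outcome tests name no covariate; prespecified baseline adjustment would be the better choice

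*Protocol article*

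**What the plan says.** The Statistical analysis section names one method for baseline data: the patients' "descriptive characteristics are compared using the Chi-square test in the study and control groups". The sentence neither lists the characteristics nor limits the test to categorical ones. One continuous characteristic appears elsewhere: eligibility is for "patients aged 18 to 60 years old with elective LC".

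For outcomes, the section names paired and independent t tests; the sentence ends "test are utilized to compare the patients’ values between the 2 groups". It adds: "Variance analysis was utilized to compare the repeated measurements". No covariate is named for any of these. A single threshold, P "< .05 is regarded the significant in statistics", covers the whole section.

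On allocation, the Subjects section gives 100 patients per arm and says that "all participants will be assigned a random number via utilizing the random number table", with no mention of stratification. The Intervention section states: "The primary outcomes include State-Trait Anxiety level and postoperative visual analogue scale". Both are scores.

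**The concern.** A significance test of baseline differences between randomised arms asks whether those differences arose by chance. If the randomisation was carried out properly, the answer is known in advance. The useful question is whether an imbalance in a prognostic variable is large enough to move the outcome comparison. A P value does not answer that in either direction.

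The stated outcome tests do not make up for this. A between-group t test without covariates carries any chance imbalance in a prognostic variable into the estimated effect, in proportion to the correlation between that variable and the outcome. It also leaves the variance that the variable explains in the error term. The Chi-square test is therefore the only comparability check the article names, and it does nothing to the outcome analysis. At stake are precision and the trustworthiness of the estimate given the imbalance that actually occurs.

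**Working it through.** The article gives no effect size, SD or power, so there is no plan figure to reproduce.

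**Inputs from the article:** 100 per arm; threshold .05; age range 18 to 60; t tests and variance analysis with no covariate named.

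**Assumptions, not in the article:** two-sided test; effect of 0.3 or 0.4 SD; baseline-outcome correlation ρ of 0.3, 0.5 or 0.7; for the age simulation, mean 42 and SD 10, rounded to whole years and held within 18 to 60.

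**1. Chi-square on a continuous characteristic.** Single years from 18 to 60 give 60 − 18 + 1 = 43 categories, so the average expected count per cell is 100/43 = 2.3. In 4,000 simulated trials per setting, the share with P < .05 was:

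| True age shift | t test | Chi-square, single years | Chi-square, four bands | Chi-square, two-way split |
|---|---|---|---|---|
| 0 | 5.2% | 2.5% | 5.0% | 5.9% |
| 0.4 SD | 78.6% | 11.7% | 56.3% | 60.2% |

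Banding makes Chi-square usable but wastes information. Single years make it unreliable: about 90% of cells have an expected count below 5.

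**2. What the baseline tests can show.** With k independent tests at .05, the chance of at least one significant difference under correct randomisation is 1 − 0.95^k. This is 22.6% for k = 5 and 40.1% for k = 10. The article gives no k, so these values are illustrative.

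**3. What a non-significant test leaves.** The standard error of a baseline difference, in SD units, is √(2/100) = 0.141. A difference up to 1.96 × 0.141 = 0.277 SD is non-significant. A baseline difference D shifts the unadjusted outcome difference by ρD. With no treatment effect, the type I error given D is Φ((−1.96 − s)/√(1−ρ²)) + 1 − Φ((1.96 − s)/√(1−ρ²)), where s = ρD/0.141.

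| D (baseline P) | ρ = 0.3: shift, error | ρ = 0.5: shift, error | ρ = 0.7: shift, error |
|---|---|---|---|
| 0.10 SD (0.48) | 0.03 SD, 4.5% | 0.05 SD, 3.6% | 0.07 SD, 2.0% |
| 0.20 SD (0.157) | 0.06 SD, 6.0% | 0.10 SD, 7.5% | 0.14 SD, 8.7% |
| 0.277 SD (0.05) | 0.08 SD, 7.9% | 0.14 SD, 12.9% | 0.19 SD, 20.5% |

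The first row is close to typical: the median absolute imbalance is 0.674 × 0.141 = 0.095 SD. The last row is the extreme of the non-significant range. Error below 5% at small imbalances offsets error above 5% at large ones, so the average over randomisations is 5%.

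**4. What adjustment gains.** ANCOVA reduces the residual SD to √(1−ρ²), so power is Φ(d/(0.141 × √(1−ρ²)) − 1.96). For d = 0.4, unadjusted: 0.4/0.1414 = 2.83, and Φ(0.87) = 80.7%. For d = 0.4 and ρ = 0.5: 2.83/0.866 = 3.27, and Φ(1.31) = 90.4%.

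| Effect | Unadjusted | ρ = 0.3 | ρ = 0.5 | ρ = 0.7 |
|---|---|---|---|---|
| 0.3 SD | 56.4% | 60.4% | 68.8% | 84.4% |
| 0.4 SD | 80.7% | 84.3% | 90.4% | 97.7% |

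**5. Is there a baseline anxiety score to adjust for?** The Intervention section describes the visit and then the assessments, and does not clearly place an anxiety measurement before the visit in both arms. The paired t test and the repeated-measures analysis imply an earlier measurement, but only by implication.

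**The case against.** A reader might infer that every characteristic, age included, will be put through a Chi-square test and that the planned test is simply wrong. The text does not support that. It does not say that all characteristics are tested this way, it lists none, and age appears only as an eligibility limit. Chi-square is correct for categorical characteristics and valid for age bands, and the t tests on patients' values may have been meant to cover continuous baseline variables. What remains is that the sentence sets no such limit.

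A reader might also infer that the outcome comparison is invalid. It is not: randomisation makes the unadjusted t test unbiased, with the correct type I error on average. No decision in the article depends on a baseline P value, so deleting those tests would by itself change no trial result.

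It can further be argued that a covariate list belongs in an analysis plan that is not shown. Its absence alone would indeed be no finding. But the article states which comparisons will be made, and these name no covariate; proposing a better method for a stated comparison is a different matter.

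Finally, the size of the gain depends on assumed correlations. This objection stands. Nothing in the article supports a high correlation between baseline anxiety and postoperative pain, and age and sex alone may explain little.

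**Conclusion.** The concern holds in limited form. The stated baseline tests are uninformative about comparability in a randomised trial and poorly suited to any unbanded continuous characteristic, while the stated outcome tests forgo an available gain. For a 0.4 SD effect that gain is roughly 4 to 17 percentage points of power across correlations of 0.3 to 0.7, together with removal of the shift caused by chance imbalance in the adjusted covariates. At the median imbalance this shift is about 0.03 to 0.07 SD (0.095 × 0.3 to 0.095 × 0.7). The figures rest on a two-sided test, full data on 100 per arm, a linear baseline-outcome relation and the assumed effects and correlations. Severity is minor to moderate.

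**What to change.** - Drop the between-arm tests of descriptive characteristics. Summarise baseline by arm without P values: mean and SD or median and quartiles for continuous variables, counts and percentages for categorical ones. Keep Chi-square or Fisher's exact test for categorical outcomes.
- Replace the between-group t tests of the primary outcomes with ANCOVA, or a mixed model where measurements are repeated. Adjust for covariates fixed before allocation, whatever imbalance is observed: age and sex.
- Add the anxiety score as a covariate only if it is measured before the visit in both arms, and state that timing. A post-visit score must not be used, because adjusting for it would remove part of the effect under study.

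For age and sex the cost is a change of wording and slightly more analysis work, assuming both are recorded; the article does not mention sex. If no pre-visit anxiety score is currently collected, adding one means an extra assessment in both arms, which goes beyond wording.

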### Study design

2.1

This is a single center, placebo-controlled randomized trial that will be performed from August 2020 to December 2020. The trial is performed in accordance with the SPIRIT Checklist for randomized studies. It is authorized by the Ethics Committee of Taizhou Hospital of Zhejiang Province (D20211-34) and then is registered in research registry (researchregistry5924). The surgeon will explain the details of trial, afterward, patiently answer all the questions from patients. These patients are then presented with the written information of our trial. Each patient receives a written informed consent. As all patients participated voluntarily, they could withdraw at any time during the trial.

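### Classical variance analysis and paired t tests discard patients with incomplete series although withdrawal is open; for repeated outcomes, a mixed model on all observed values is a cheap improvement

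*Protocol article*

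**What the plan says.** The protocol article, Statistical analysis (section 2.5), names its methods in a few lines. On software: "For data analysis, the SPSS 20.0 is employed". On outcome values: "Paired-samples *t* test and independent samples *t* test are utilized to compare" the two groups. On series: "Variance analysis was utilized to compare the repeated measurements". The threshold is "A *P* < .05 is regarded the significant in statistics".

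Study design (section 2.1) says of patients that "they could withdraw at any time during the trial". Subjects (section 2.3) sets the size: "Two hundred patients undergoing LC will be included in this study", 100 per arm. Intervention (section 2.4) gives the endpoints: "The primary outcomes include State-Trait Anxiety level and postoperative visual analogue scale".

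The article does not say which outcomes are repeated or when, and gives no expected withdrawal rate. Section 2.4 mentions a 30-minute period for the assessments, in wording that is hard to interpret.

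**The concern.** Classical repeated-measures analysis of variance needs a full row of measurements for each patient. One missing time point removes the patient, including the values already recorded. A paired t test does the same for an incomplete pair. Since withdrawal is open at any time, the two methods named for within-patient data rest on completers as soon as anyone leaves midway.

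The setting makes selective withdrawal plausible. Patients know whether they had the nursing visit, the primary outcomes are their own reports of anxiety and pain, and anxiety is itself a possible reason to decline a later questionnaire. If unvisited anxious patients leave more readily than visited ones, the completers in the two arms are no longer comparable. The repeated-measures contrast can then be biased, and valid early measurements are lost.

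**Working it through.** **Inputs from the article.** 100 patients per arm; P < .05 (two-sided assumed); the three methods named; withdrawal allowed. There is no power, effect size, SD or dropout figure to reproduce. Everything else below is an assumption chosen to show a range.

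**1. What each named method does with a patient who leaves midway.**
- Classical repeated-measures variance analysis: the patient is dropped entirely.
- Paired t test: the patient is dropped if either value is missing.
- Independent t test: the patient is kept at every time with a value. At a time after withdrawal the patient is absent, as from any simple two-group comparison.

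**2. Patients lost.** With a share q missing independently at each of T time points, the complete share is (1 − q)^T. For q = 5%:
- T = 2: 0.95² = 90.2%
- T = 3: 0.95³ = 85.7%
- T = 4: 0.95⁴ = 81.5%, so 18.5% are lost

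This formula describes intermittent gaps. Pure withdrawal, where a patient who leaves stays away, follows a different pattern.

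**3. Power.** With 100 per arm, a two-sample comparison has 80.7% power for 0.40 SD. It has 78.7% with 5% lost, 76.5% with 10% and 71.6% with 20%. These falls compare with having no missing data, so they are not what a mixed model would recover. In simulations with completely random withdrawal and two time points, the model's gain over complete cases was:
- 5% withdrawal, final value: 75.7% to 76.5% (0.8 points); change: 85.7% to 86.7% (1.0)
- 15% withdrawal, final value: 72.8% to 75.3% (2.5 points); change: 81.2% to 83.2% (2.0)

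**4. Bias, mild example.** Assume a true effect of −0.40 SD at both of two assessments and correlation 0.6. Of patients above +0.5 SD at the first assessment, 30% of controls and 10% of visited patients withdraw.
- Loss: controls 0.30 × 0.309 = 9.3%; visited 0.10 × 0.184 = 1.8%; mean 5.5%.
- Shift in the retained first score: controls −0.30 × 0.352 / 0.907 = −0.116; visited −0.10 × 0.266 / 0.982 = −0.027 (0.352 and 0.266 are normal densities at 0.5 and 0.9).
- Second assessment, completers: (−0.40 − 0.6 × 0.027) − (−0.6 × 0.116) = −0.416 + 0.070 = −0.346.

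Simulation of 3,000 trials gave −0.350 for completers and −0.404 for the likelihood estimate. The bias of 0.05 SD is about a third of the standard error, √(2/100) = 0.14.

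**5. Bias, harsher example.** 15% withdrawal depending on the previous score, in opposite directions by arm; effect −0.40 SD after baseline; correlation 0.6; two time points; 600 replicates.
- Final value: completers −0.27, mixed model −0.40. With no true effect, they reject in 13.3% and 6.5% of trials.
- Change from baseline (the arm-by-time contrast): completers −0.48, mixed model −0.40. With no true effect, 8.2% and 5.5%.

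The two errors agree with each other. A final-value bias of 0.132 implies a baseline imbalance of 0.132 / 0.6 = 0.22, hence a change bias of 0.132 − 0.22 = −0.088, against −0.084 simulated. The direction of the error therefore depends on the contrast reported. Four time points (300 replicates) gave −0.26 against −0.38 for the final value and −0.42 against −0.39 for change; Monte Carlo error is about 0.14 / √300 = 0.01.

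**6. Where the model helps little or not at all.**
- Withdrawal related to earlier scores in the same way in both arms (15%, two time points): completers −0.406, model −0.403. Neither contrast is biased.
- Withdrawal depending on the unseen value itself, opposite by arm, 15%: the model gives −0.26 (two time points) or −0.33 (four) for the final value, with 16% and 7% false rejections. For change from baseline it is further from −0.40 than completers: −0.27 against −0.32, and −0.33 against −0.37.

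**The case against.** The strongest reply is that this is a missing-data omission presented as a stated method. The article names variance analysis without a procedure, factors or a rule for missing values, and never says incomplete patients are excluded. Such rules commonly sit in a full protocol or SAP, which is not shown. This stands in part: completers-only analysis follows from the usual form of the methods and is not written down. But the methods themselves are written down, and none of them uses a partial series, so the choice of method can fairly be criticised.

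A reader might infer that the whole analysis is completers-only. The article does not support that. The independent t test is also named, is the natural tool for comparing arms, and does not discard a patient for a gap elsewhere. Its limit is only that, at a late time, it too lacks those who have already left.

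A reader might also infer that a mixed model removes the problem at no cost. It does not. It assumes missing at random, can be biased when that fails, and adds nothing for a patient with no outcome value. An outcome measured once without a baseline gains nothing either. Postoperative pain has no natural pre-visit value, and section 2.4 does not clearly schedule a pre-visit anxiety score or a primary time.

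Finally, the loss may be small. No rate is stated, and assessment over about 30 minutes in hospital leaves little time to drop out. This stands, and it limits the weight of the point.

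**Conclusion.** The point holds for the variance analysis and the paired t tests, and only for outcomes measured more than once. In classical form both discard patients with incomplete data in a trial that permits withdrawal at any time. Bias in the between-arm contrast needs withdrawal that relates to earlier scores and differs by arm; otherwise the harm is a modest loss of information.

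The actual size cannot be known from the article. Under the assumptions shown, bias runs from none, through 0.05 SD at 5.5% loss, to about 0.13 SD at 15% loss in a deliberately adverse pattern. A mixed model corrects this when data are missing at random. The fall in power from about 80% to 72–77% that one can calculate for 9–19% loss should not be read as what the model would restore; under random loss the gain is about 1 to 2.5 points. This is a cheap improvement and does not show that the planned comparison is invalid.

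**What to change.** For each outcome measured more than once, list the time points and name one primary time. Replace the variance analysis and paired tests with a linear mixed model on all observed values of all randomised patients, analysed as allocated. Include arm, time and arm-by-time with an unstructured covariance, plus the pre-visit score where one is collected. Report the between-arm contrast at the primary time with its confidence interval. State the missing-at-random assumption and add a sensitivity analysis for data not missing at random, for example by shifting unobserved values by a range of amounts in each arm. Outcomes measured once stay with a two-group comparison.

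The cost is a few sentences in the analysis section and a little programming; the MIXED procedure in the SPSS version already named fits this model. No extra patients are needed. The downsides are reliance on missing at random and the need for a fixed set of time points.

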## Results

3

Figure 1 shows the comparison of outcomes between 2 groups.

**Figure 1 F1:**
[figure not shown]
The comparison of outcomes between 2 groups.

## Discussion

4

The purpose of this study is to study the influences of preoperative nursing visit against the anxiety and complications after operation in the patients receiving LC. Anxiety is a kind of emotional disorder caused by acute conditions or trigger. It is manifested in the components of the autonomic nervous system, for instance, stress, anxiety, nervosity, and discomfort. Most patients with anxiety are more active, nervous, and alert to various stimuli.^[14,15]^ Inappropriate management of early postoperative anxiety will not only prolong recovery but also increase the risk of other complications.^[16,17]^ Laurion et al^[18]^ have reported that the music therapy decreased the postoperative pain, nausea, and vomiting, and reduces the pain in women undergoing laparoscopic surgery. The informative and supportive preoperative nursing visits can make patients better perceive the surgery, anesthesia, as well as rehabilitation. There is evidence that the beneficial effects of preoperative care visits on the physical recovery and complications after operation are direct rather than long-term. Although this study can provide evidence of the effect of preoperative nursing visit in patients with LC, due to the small sample size, high-quality research is still required.

## Conclusion

5

The preoperative nursing visit may decrease the anxiety and the complications after operation in patients receiving LC.

## Abbreviations

Abbreviations: LC = laparoscopic cholecystectomy, VAS = visual analog scale.
